### CBE and CSE stent

The CBE stent used in our trial is BARD® LIFESTREAM™ Covered Stent, a permanent stent used to maintain patency of the common or external iliac artery. The stent is a balloon-expandable stent with expanded polytetrafluoroethylene (ePTFE) encapsulated between two layers (inner and outer). The implant is pre-mounted on an over-the-wire balloon catheter that acts as the delivery system. The configurations of BARD® LIFESTREAM™ covered stent offered 16, 26, 37, 38, and 58 mm in length and 5 to 12 mm in diameter. The stents can be overlapped if the target lesion exceeds the longest available length of stent.

GORE® VIABAHN™ self-expandable covered stent is the only CSE stent adopted in our trial; it consists of two main components: an intravascular covered stent and a catheter-based delivery system. The stent consists of a self-expanding nickel-titanium alloy stent combined with an ePTFE intracavity coating, which is offered in lengths of 25, 50, and 100 mm and in diameters of 5 to 11 and 12 mm in the configurations.

### Follow-up and outcomes of interest

Primary outcome and secondary outcomes are set based on patient-centered outcomes. All included patients will be followed up in outpatient clinics using questionnaires at 1 month, 6 months, 12 months, 24 months, and 36 months after the initial intervention. Patients who are unable to return will be followed up on telephone. Duplex ultrasound will be tested routinely at 1, 6, 12, 24, and 36 months post-index procedure; CTA will be routinely tested at 12 and 36 months post-index procedure; and if duplex US suggests restenosis at the target lesion, a further CTA examination will be performed to assess the stenosis. If the restenosis is more than 50% and the patient’s symptoms are worse (e.g., shorter claudication distance or exacerbation of pain), reintervention will be carried out. Patients who are unable to return to clinic will be suggested to undergo computed tomography angiography (CTA) or duplex ultrasonography in local hospital. Images and medical records will be sent to investigators online. Trained outcomes assessor will collect the outcomes of interest, blinded to the intervention groups.

The timepoint for the primary outcome of this study is 12 months. Patients are defined as dropout if they meet the following criteria: (1) lost to follow-up for less than 12 months post-intervention: a subject is considered loss to follow-up if cannot be contacted via fifth attempts by telephone and WeChat message. (2) Withdrawal consent to participation of the study: all participants have the right to withdraw from the study at any time for any reason.

#### Primary outcome

Target lesion revascularization (TLR) of the target lesion(s) assessed at 12 months after the intervention (TLR is defined as the first revascularization procedure (e.g., percutaneous transluminal angioplasty (PTA), atherectomy, and catheter-directed thrombolysis)) when the primary patency is lost.

#### Secondary outcomes

The following secondary endpoints of this study are collected at 1, 6, 12, 24, and 36 months post-index procedure:

(1) Stent and/or surgery related mortality; (2) all-cause mortality; (3) amputation-free survival; (4) acute limb ischemia rate; (5) major adverse cardiovascular and cerebrovascular events (MACCEs); (6) target vessel revascularization (TVR) (TVR is defined as the first revascularization procedure (e.g. PTA, stenting, surgical bypass, etc.) in the target vessel(s)); (7) primary patency (the loss of primary patency is defined as target lesion(s) is determined to be > 50% stenosis or TLR/TLR needed in follow up); (8) primary assisted patency (the loss of primary assisted patency is defined as target lesion(s) is determined to be > 50% stenosis after TLR); (9) secondary patency (the loss of secondary patency is defined as target lesion(s) is determined to be > 50% stenosis after endovascular procedure or surgical bypass TVR); and (10) stent-related complication (e.g., stent kinking or fracture).

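### As defined, secondary patency cannot credit rescue after a failed endovascular TLR: it equals primary assisted patency, or falls below it, instead of sitting at or above it

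*Protocol article*

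**What the plan says.** Three patency endpoints are listed in the protocol article under Secondary outcomes, in the order primary, primary assisted, secondary.

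- For primary patency, item 7 reads: "the loss of primary patency is defined as target lesion(s) is determined to be > 50% stenosis or TLR/TLR needed in follow up".
- For primary assisted patency, item 8 reads: "the loss of primary assisted patency is defined as target lesion(s) is determined to be > 50% stenosis after TLR".
- For secondary patency, item 9 reads: "the loss of secondary patency is defined as target lesion(s) is determined to be > 50% stenosis after endovascular procedure or surgical bypass TVR".

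TLR is defined under Primary outcome as the first revascularization once primary patency is lost. Its examples are "percutaneous transluminal angioplasty (PTA), atherectomy, and catheter-directed thrombolysis". Target vessel revascularization (TVR) is defined in item 6 by location in the vessel, with PTA, stenting and bypass as examples. On timing: "The following secondary endpoints of this study are collected at 1, 6, 12, 24, and 36 months post-index procedure". The article does not say whether a patency loss is final once it has occurred or whether status is read afresh at each visit.

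**The concern.** The order of the three endpoints implies a hierarchy. Primary patency should be the strictest, assisted patency should give credit for a maintaining reintervention, and secondary patency should give credit for further rescue. For any lesion at any visit this means primary ≤ assisted ≤ secondary.

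Item 9 does not achieve this. It does not require assisted patency to be lost first, and it has no clause that lets a later successful procedure preserve secondary patency. It repeats item 8 with a wider list of preceding procedures, so it offers more ways to fail.

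The trial compares two stent types with a stated interest in midterm and long-term results. Whether a failed stent can be rescued is the question secondary patency exists to answer, and the endpoint as written cannot answer it. The Statistical analysis section also tests secondary outcomes for superiority once noninferiority is reached, and applies a Hochberg adjustment to the endpoints. Two of the ten secondary endpoints in that set would be duplicates, or would stand in an order their names contradict.

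**Working it through.** There is no stated figure to reproduce, because the point is one of set inclusion.

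**Step 1: compare the definitions.** Let A be loss of assisted patency and S loss of secondary patency.

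| | Lesion | Threshold | Preceding procedure required |
|---|---|---|---|
| A (item 8) | target lesion | > 50% stenosis | TLR |
| S (item 9) | target lesion | > 50% stenosis | endovascular procedure, or surgical bypass TVR |

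Only the last column differs. Every TLR example is endovascular, so for an endovascular TLR the condition for A is contained in the condition for S. Reading TVR as qualifying both procedures in item 9 does not change this. A TLR takes place in the target vessel, so either it is itself the first TVR, or an earlier endovascular or bypass TVR has already met the condition for S.

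**Step 2: enumerate.** Each history has five steps. Each step is imaging at ≤ 50%, imaging at > 50%, or one of the allowed procedures. With one procedure type there are 3^5 = 243 histories; with three there are 5^5 = 3,125. The definitions were coded literally under two readings: the first loss is final, or status is taken at the last imaging.

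| Procedures allowed | Reading | A and S lost | A lost, S kept | S lost, A kept |
|---|---|---|---|---|
| Endovascular TLR only (243) | first loss final | 131 | 0 | 0 |
| | last imaging | 90 | 0 | 0 |
| Endovascular TLR, TVR away from the lesion, bypass (3,125) | first loss final | 821 | 0 | 784 |
| | last imaging | 660 | 0 | 570 |
| Endovascular TLR, open non-bypass TLR, bypass (3,125) | first loss final | 1,035 | 285 | 285 |
| | last imaging | 842 | 194 | 194 |

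These are counts of possible patterns, not probabilities. In the first set the endpoints coincide. In the second, secondary patency is never above assisted and is sometimes below it. Only the third set, which contains a TLR type the article does not list, produces histories with A lost and S kept.

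**Step 3: individual histories.**

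- Stenosis, TLR, stays open: neither is lost, on either reading.
- Stenosis, TLR, > 50% again, second endovascular procedure, open: both are lost if the first loss is final. If status is read at the last imaging, neither is lost. On neither reading does secondary patency credit more than assisted.
- Stenosis, bypass, native lesion still > 50%: S is lost and A is kept on both readings, even if the bypass is open.
- Stenosis > 50%, never treated: primary patency is lost, but neither A nor S is, because both require a prior procedure. This can occur, since the Follow-up section ties reintervention to worsening symptoms as well as restenosis.

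**Step 4: size.** The nearest figures are the planning patencies in the Sample size section. They imply 53 × (1 − 0.891) = 5.8 and 53 × (1 − 0.822) = 9.4 lesions per arm losing primary patency by 9 months. Any lesion that meets S has also lost primary patency, so these are outer limits at 9 months if the planning values hold. The 53 includes the 15% dropout allowance, so evaluable numbers would be lower. The document gives no share of these lesions that receive TLR, restenose, undergo TVR elsewhere or are bypassed, so the number affected cannot be obtained.

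**The case against.** The strongest reply is that the definitions can be read in sequence: TLR is the first procedure, assisted patency covers what follows it, and secondary patency covers what follows the next endovascular procedure or bypass. That is probably the intention, but item 9 does not say so. Nor is this detail left to a fuller document, because both definitions are stated here and the fault lies in what they state.

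Other parts of the reply stand, and they limit the point.

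- A reader might infer that secondary patency can never exceed assisted patency. The TLR examples are introduced by *e.g.*, so an open, non-bypass TLR is possible and breaks the inclusion, as the third set in the table shows.
- A reader might infer that the hierarchy is always inverted. With endovascular TLR only, the endpoints are identical. Inversion needs a TVR away from the lesion, or a bypass, followed by > 50% stenosis of the target lesion.
- A reader might infer that successful rescue is generally counted as failure. A first TLR that stays open keeps both patencies. A successful repeat procedure after a failed TLR counts as a failure only if the first loss is final, which the article does not state. The bypass case fails on either reading.
- A reader might infer that a rescued occlusion is wrongly counted as assisted-patent. The document does not use occlusion versus stenosis to separate the endpoints, and it lists catheter-directed thrombolysis as a TLR.

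**Conclusion.** Wrong as written, for two of the ten secondary endpoints. For endovascular TLR, loss of assisted patency always entails loss of secondary patency, so secondary patency is equal to or lower than assisted patency. It cannot credit further rescue after a failed TLR if the first loss is final. If status is read at each visit, it still adds nothing beyond assisted patency in that case.

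The conclusion rests on the literal wording and on TLR being endovascular, as in every example given. Only lesions that undergo a procedure during follow-up are affected; their number is unknown and may be small. A reader might infer that these endpoints are wrong throughout, or that a particular number of lesions per arm is misclassified. The document supports neither. The primary TLR endpoint and the sample size do not depend on items 8 and 9. The change is worth making because the trial was still recruiting when the article was written and the correction costs little.

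**What to change.** 1. Reword item 9 so that secondary patency is lost only when assisted patency has already been lost and > 50% stenosis or occlusion of the target lesion is not restored by a later procedure. Remove restenosis after an endovascular procedure as a loss in itself.
2. State whether each patency endpoint is a first loss or a status at each visit. The choice matters: if assisted patency is itself re-read at each visit, it also recovers after a successful second procedure, and the two endpoints coincide again for endovascular histories.
3. State one rule for untreated lesions and one for bypassed lesions, and apply each to both items 8 and 9. Changing item 9 alone could leave an untreated or bypassed stenosis that keeps assisted patency but loses secondary patency.
4. Reconcile the wording with the TLR definition under Primary outcome, including whether an open, non-bypass procedure at the lesion counts as TLR.
5. Add a programmed check that primary ≤ assisted ≤ secondary holds for every lesion at every visit.

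The cost is two reworded definitions, one consistency check, and a case report form entry for the result of each reintervention. No extra patients or visits are needed.

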### Data collection and management

Two investigators will use a pre-identified and unified case report form (CRF) to record the data of included patients independently. Both received training for data collection. Demographics, comorbidities, and prescriptions of cardiovascular drugs were recorded from patient chart. Imaging anatomic parameters were measured from picture archiving and communication system (PACS). Laboratory results were collected from laboratory information system (LIS).

As for data management, two investigators retrieved data from CRF and recorded them in two identical electronic forms, and cross check will be performed to ascertain the accuracy of data. We also set range checks for data values. Importantly, the investigators will be urged to follow up on patients by telephone contacts. Data will be collected in as much detail as possible. Collected data lists will be de-identified and stored in monitoring committee and will be made available to the third-party regulatory body upon request.

### Sample size calculation

We calculated the sample size for this study based on the results of previous studies [4, 13]. As is reported previously in AIOD patients, the 9-month primary patency of CBE stent (BARD®LIFESTREAM™ Stent) was 89.1%, while the 9-month primary patency of the CSE stent (GORE® VIABAHN™ stent) was estimated to be 82.2% based on VIASTAR Trial [14, 15]. In the present study, we hypothesized that the primary patency of CBE stent is not inferior to that of CSE stent; the predetermined noninferiority margin on risk difference scale (δ) is set as 10% between treatment groups. The type I error rate is 0.05, the power of the test is set as 80%, and the randomization ratio is set as 1:1. After accounting for a 15% dropout rate. It was calculated that 53 lesions per group are needed for a total of 106 lesions.

In order to achieve adequate participant enrollment, we will recruit patients by putting up posters or advertising on the Internet, furthermore, we actively recruit patients from outpatient department and emergency department.

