**Methods:**

This trial is a prospective, single-center, parallel, noninferiority, randomized controlled trial. A total of 106 patients will be enrolled and these patients will be randomized to either the CBE stent group or the CSE stent group. The primary end point of the study is the occurrence of target lesion revascularization (TLR) at 12 months after the intervention.

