## Discussion

The past three decades have witnessed open surgery shift to endovascular strategies as the preferred treatment for mild-to-moderate-to-severe AIOD. Endovascular therapy is increasingly preferred as the first-line treatment in most AIOD patients. Different stents have different designs (covered stents, bare metal stents, self-expanding stents and balloon-expandable stents) but which type is the best for AIOD patients has yet to be fully elucidated [17].

Previous studies have shown that covered stents can create a smooth hemodynamically favorable lumen and resist hyperplastic ingrowth through BMS interstices; in addition, covered stents can also protect against iliac artery rupture post-dilation [8, 10, 18]. Self-expandable stents have high elasticity and small radial force, which helped to prevent circumferential stress and subsequently enhanced neointimal proliferation. This may be the reason why self-expandable bare metal stents led to a decreased incidence of restenosis at 12 months compared with treatment with balloon-expandable bare metal stents [9]. However, the best choice between CBE stent and CSE stent is left to the interventionalist’s preference and lack of RCT data now, leading to there is no consensus or relevant guidelines on which stents should be used in AIOD.

The Viabahn stent and LifeStream stent represent one of the most widely used CSE and CBE stents, respectively. A previous study showed that Viabahn covered stent can be considered an acceptable patency with low complications during the long-term period in low-risk young AIOD patients [4], especially for complex aortoiliac occlusion lesions [19]. Another study indicated that the LifeStream stent provided satisfactory 9-month clinical outcomes, including a low rate of TLR for the treatment of stenotic and occlusive lesions of the iliac arteries [15]. However, there is no long-term period patency or TLR of the LifeStream stent. Furthermore, there is no cohort or RCT study to compare the efficacy or effect between Viabahn stent and LifeStream stent. The main aim of our present trial is to compare TLR of the target lesion of LifeStream stent with Viabahn at 12 months’ follow-up.

In conclusion, this trial was designed to compare the efficacy and safety of a CBE stent (BARD®LIFESTREAM™) versus a CSE stent (GORE® VIABAHN™) in AIOD patients, hoping to provide level 1 evidence for stent selection in aortoiliac occlusive lesions.

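### The sample size, noninferiority hypothesis and margin rest on 9-month primary patency, but the primary endpoint is 12-month TLR, for which no rate, power or margin rationale is given

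*Protocol article*

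**What the plan says.** The protocol article names its primary endpoint consistently. The abstract says "The primary end point of the study is the occurrence of target lesion revascularization (TLR) at 12 months after the intervention". The Primary outcome section has "Target lesion revascularization (TLR) of the target lesion(s) assessed at 12 months after the intervention", and Follow-up and outcomes of interest confirms that "The timepoint for the primary outcome of this study is 12 months".

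The Sample size calculation section uses a different endpoint and a different time. Its planning rates are 9-month primary patency for both stents ("Stent) was 89.1%, while the 9-month primary patency of the CSE stent" was put at 82.2%). Its hypothesis is "we hypothesized that the primary patency of CBE stent is not inferior to that of CSE stent", and the 10-point risk-difference margin is set in the same sentence. The other inputs are a type I error of 0.05 with no sidedness given, 80% power, 1:1 allocation and 15% dropout. The result is 53 lesions per group, 106 in total.

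Primary patency is item (7) under Secondary outcomes, where "the loss of primary patency is defined as target lesion(s) is determined to be > 50% stenosis or TLR/TLR needed in follow up". The Statistical analysis section repeats the 10-point margin for the absolute difference between groups and names no endpoint. The Protocol amendments section says that the sample size may be adjusted on 12-month TLR, with no assumed rate and no rule. No numerical TLR rate for either stent appears anywhere. The Discussion says only that a study of the LifeStream stent found "satisfactory 9-month clinical outcomes, including a low rate of TLR".

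**The concern.** A noninferiority trial rests on a hypothesis, an expected rate in each group and a margin, all for the primary endpoint. Here all three are written for a secondary endpoint at an earlier time. The two endpoints are not interchangeable: restenosis above 50% counts as loss of patency even if no procedure follows, whereas TLR is a procedure done once patency is lost.

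Two things are at stake. The first is power: a reader will take 80% as the chance of showing noninferiority on TLR, and the document does not support that. The second is the margin: a fixed 10-point difference permits a larger relative increase the rarer the event is, so a margin chosen against a 17.8% failure rate may be lenient for TLR.

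**Working it through.** **Inputs from the document.** Patency 0.891 (CBE) and 0.822 (CSE), so patency loss is 0.109 and 0.178. Margin 0.10, power 0.80, type I error 0.05, 53 per group. Because sidedness is not stated, one-sided 0.05 and 0.025 are both shown (z = 1.645 and 1.960; z for 80% power = 0.842).

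**Step 1: reproduce the plan's figure.**

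n = [p1(1−p1) + p2(1−p2)] × (z_α + z_β)² / (margin + advantage)²

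- Variance sum: 0.891×0.109 + 0.822×0.178 = 0.0971 + 0.1463 = 0.2434
- Distance to the margin: 0.10 + (0.891 − 0.822) = 0.169
- One-sided 0.05: 0.2434 × (1.645 + 0.842)² / 0.169² = 52.7, so 53 per group before dropout
- One-sided 0.025: 66.9, so 67 per group before dropout

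The figure 53 is thus reproduced from the 9-month patency rates at one-sided 0.05, before any allowance for dropout.

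**Step 2: power of 53 evaluable per group for 12-month TLR.** The document gives no TLR rate, so all rates below are assumptions. Holding n at 53 keeps the dropout question out of the comparison.

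Power = Φ[(0.10 + p_CSE − p_CBE) / √{[p_CBE(1−p_CBE) + p_CSE(1−p_CSE)] / 53} − z_α]

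Example, 5% in both groups: SE = √(0.095/53) = 0.0423; 0.10/0.0423 = 2.362; Φ(2.362 − 1.645) = 0.763.

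| Endpoint and rates (CBE vs CSE) | One-sided 0.05 | One-sided 0.025 |
|---|---|---|
| Patency loss as planned, 10.9% vs 17.8% | 0.802 | 0.703 |
| TLR 3% vs 3% | 0.915 | 0.855 |
| TLR 5% vs 5% | 0.763 | 0.656 |
| TLR 10% vs 10% | 0.528 | 0.404 |
| TLR 15% vs 15% | 0.419 | 0.302 |
| TLR 5% vs 10% | 0.903 | 0.838 |
| TLR at half of patency loss, 5.45% vs 8.9% | 0.852 | 0.767 |

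Power falls on both sides of the stated 80%. It depends on the TLR rate and on whether CBE is assumed to be better. The normal approximation is rough at the lowest rates: 3% to 5% of 53 is about 2 to 3 events per group.

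**Step 3: what the margin permits.** Permitted relative risk = (control rate + 0.10) / control rate.

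- Planning patency loss, 17.8%: 0.278/0.178 = 1.56
- TLR 10%: 0.20/0.10 = 2.0
- TLR 5%: 0.15/0.05 = 3.0

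**Step 4: how the endpoints relate.** By the definitions under Primary outcome and Secondary outcomes, TLR is a procedure done when patency is lost, and TLR itself counts as loss of patency. At any one time, therefore, TLR cannot exceed loss of patency. That ordering does not carry across times: 12-month TLR and 9-month patency loss cannot be strictly ranked.

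**The case against.** Four points can be made for the plan.

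**A rarer endpoint need not cost power.** This stands. Halving the planned patency-loss rates raises power at n = 53 from 0.802 to 0.852. The low values in the table come mostly from dropping the assumed CBE advantage, which would hurt patency too: at 17.8% loss in both groups, power is 0.382. A reader might infer that the trial is underpowered for TLR. The document does not show that; it shows only that the power for TLR is unknown.

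**The margin does cover TLR.** In a nominal sense it does, since the Statistical analysis section restates 10 points in the paragraph that governs the primary and secondary endpoints. To say that the margin does not apply to TLR would go too far. What is missing is any reason for 10 points on that endpoint.

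**The sample size can be adjusted on 12-month TLR.** The Protocol amendments section allows this, and it is the only text that ties the size to the primary endpoint. With no assumed rate, target or rule, it does not supply the missing power.

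**TLR need not be smaller or purely symptom-driven.** A reader might infer that both the TLR rate and the difference between stents must be below 10.9% vs 17.8%. The document does not establish this. The times differ, the low-TLR remark concerns one stent at 9 months and carries no number, and a smaller rate does not fix the difference. The follow-up rule (restenosis above 50% with worse symptoms, for instance "shorter claudication distance or exacerbation of pain), reintervention will be carried out") says when a procedure will be done; it does not say that none is done otherwise.

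Nor does the text contain two competing written hypotheses. It contains one, on patency, beside a primary endpoint that has none.

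**Conclusion.** The mismatch is in the current text and should be corrected before the primary result is read as a noninferiority conclusion. Both endpoint and time differ, and because 53 follows from the patency rates, this is not a slip of wording. The stated 80% power belongs to 9-month patency.

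Over the assumed TLR rates, power runs from 0.42 to 0.92 at one-sided 0.05 and from 0.30 to 0.855 at one-sided 0.025, so 80% may be too high or too low. The 10-point margin has no stated rationale for TLR, and its permitted relative risk rises from 1.56 on the planning rate to 2 or 3 at control rates of 10% or 5%. These sizes rest on assumed rates and a normal approximation; the mismatch does not.

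That 53 is the number before the 15% dropout (53/0.85 = 62.4, so 63 per group) is a separate matter and is left out of the power figures here.

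**What to change.** In the Sample size calculation section:

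1. Write the hypothesis for the primary endpoint: 12-month TLR risk, CBE minus CSE, is below the margin.
2. State assumed 12-month TLR rates for both stents, with their source.
3. Restate the power that 106 lesions give over a range of those rates, with and without an assumed CBE advantage.
4. Justify the margin for TLR and report the relative risk that it permits at the assumed control rate.
5. Keep 12-month primary patency as a secondary endpoint, and label the existing 9-month calculation as applying to patency only.

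The cost is protocol wording and a recalculation. No new data are needed. The drawback is that the stated power may become less favourable.

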### Statistical analysis

R studio Version 1.2.1335 (http://www.R-project.org) and Empower (www.empowerstats.com, X&Y solutions, Inc., Boston, MA) were utilized for statistical analysis. Categorical data are expressed as numbers and rates, while continuous data are expressed as means ± standard deviation (SD) if they are normally distributed, or median (interquartile range [IQR]) vice versa. Student’s *t* test or Mann-Whitney *U* test is used for univariate analysis of continuous data, and the *χ*^2^ test or Fisher’s exact test is used for categorical data. For primary analyses, multivariate logistic regression is adopted to calculate adjusted odds ratios (ORs) and 95% confidence interval (95% CI) for short-term outcomes. Cox proportional hazard regression analysis is used to generate adjusted hazard ratio (HR) and corresponding 95% CI for long-term outcomes. The primary and secondary end points will be analyzed in the modified intention-to-treat analysis, which includes all subjects undergo randomization and subsequent interventions. Sensitivity analyses of primary and secondary endpoints are performed in the per-protocol population, based on the treatment actually received. The noninferiority margin was set at 10 percentage points for the absolute difference between groups. If the standard of noninferiority was reached, the primary and secondary outcomes were subsequently tested for superiority (*P*<0.05). Noninferiority will be considered proven if conclusions drawn from the intention-to-treat and per protocol analyses are consistent.

Further pre-specified subgroup analyses will be carried out in the following subgroups: TASC II C-D lesions versus A-B lesions, occlusion versus stenosis. Adjustment analyses for primary and secondary endpoints were performed based on the Hochberg method [16]. Multiple imputation was used to handle missing data.

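### The 53 lesions per group said to include 15% dropout is the number before dropout (at one-sided alpha 0.05); after that dropout, power under the stated patency rates is about 74%, not 80%

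*Protocol article*

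**What the plan says.** The Sample size calculation section gives all the inputs. For the balloon-expandable (CBE) stent, "the 9-month primary patency of CBE stent (BARD®LIFESTREAM™ Stent) was 89.1" percent; the self-expanding (CSE) rate "was estimated to be 82.2% based on VIASTAR Trial". The hypothesis is directional: "we hypothesized that the primary patency of CBE stent is not inferior to that of CSE stent". On the margin, "the predetermined noninferiority margin on risk difference scale (δ) is set as 10% between treatment groups". On error rates, "The type I error rate is 0.05, the power of the test is set as 80" percent, without saying whether alpha is one-sided or two-sided. Allocation is 1:1. The result follows: "After accounting for a 15% dropout rate. It was calculated that 53 lesions per group are needed for a total of 106 lesions".

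The Statistical analysis section repeats the 10-point absolute margin. It names a 95% level for "adjusted odds ratios (ORs) and 95% confidence interval (95% CI) for short-term outcomes" and for the Cox hazard ratios. It names no interval for the risk difference on which noninferiority is to be judged.

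**The concern.** The text presents 53 per group as a number that already carries a 15% dropout allowance. If so, the calculation itself must have returned about 45 evaluable lesions per group (53 × 0.85 = 45.05). The printed inputs do not appear to give so small a number; they appear to give 53 directly. In that case the allowance was announced but not applied, and the planned dropout comes straight out of the power.

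The claim that the trial has 80% power with dropout covered is at stake. The total of 106 also appears in the Abstract, and Protocol amendments allows the sample size to be adjusted, so a wrong starting figure would carry into any revision.

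**Working it through.** **Inputs** (all from Sample size calculation): CBE rate 0.891; CSE rate 0.822; margin 0.10; power 80% (z = 0.842); 1:1; dropout 15%. Alpha is 0.05 with no sidedness given, so both readings are tried: one-sided 0.05 (z = 1.645) and one-sided 0.025 (z = 1.960).

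**Reproducing 53.** The standard noninferiority formula with unpooled variance is

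n = (z_α + z_β)² × [p₁(1 − p₁) + p₂(1 − p₂)] / (difference + margin)²

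- Variance term: 0.891 × 0.109 + 0.822 × 0.178 = 0.0971 + 0.1463 = 0.2434.
- Denominator: (0.069 + 0.10)² = 0.169² = 0.02856.
- One-sided 0.05: (1.645 + 0.842)² × 0.2434 / 0.02856 = **52.7, so 53 per group, before dropout**.
- One-sided 0.025: (1.960 + 0.842)² × 0.2434 / 0.02856 = 66.9, so 67 per group, before dropout.

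**Adding 15% dropout.**

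- One-sided 0.05: 52.7 / 0.85 = 62.0, or 53 / 0.85 = 62.4, rounded up to 63. That is 62 to 63 per group (124 to 126 in total). Multiplying instead, 52.7 × 1.15 = 60.6, so 61.
- One-sided 0.025: 67 / 0.85 = 78.8, so 79 per group (158 in total).

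**Could another formula give 53 after dropout?** It would have to return about 45 before dropout. Results before dropout:

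| Variant | One-sided 0.05 | One-sided 0.025 |
|---|---|---|
| Unpooled (above) | 52.7 | 66.9 |
| Pooled variance | 53.2 | 67.6 |
| Farrington-Manning | 56.5 | 71.9 |
| Continuity-corrected | 64.0 | 78.3 |
| 82.2% variance in both arms | 63.3 | 80.4 |
| 89.1% variance in both arms | 42.0 | 53.4 |

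None gives 45. The only value below it, 42.0, inflates to 49.5 by division or 48.4 by multiplication. The 53.4 in the last column comes from a non-standard choice of variance, and it too is a figure before dropout.

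**Power.** Power = Φ(0.169 / SE − z_α), with SE = √(0.2434 / n).

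- n = 53, one-sided 0.05: SE = 0.0678; 0.169 / 0.0678 − 1.645 = 0.849; power 80.2%. The stated 80% therefore belongs to 53 evaluable lesions per group.
- n = 45, one-sided 0.05: SE = 0.0736; 0.169 / 0.0736 − 1.645 = 0.653; power **74.3%**.
- n = 45 by other methods, one-sided 0.05: exact enumeration of the Wald rule 76.9%; Farrington-Manning 71.4%.
- Conditional on a two-sided 95% interval for the margin (one-sided 0.025): 70.3% at n = 53 and 63.2% at n = 45. At n = 45, exact enumeration gives 64.3% and Farrington-Manning 59.3%.

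**The case against.** Several points on the other side are fair, and they limit the finding.

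- **The 95% interval.** A reader might infer that the planned 95% intervals fix the power at 63%, or that the sizing alpha and the decision interval contradict each other. The document does not support this. It attaches 95% intervals to odds and hazard ratios only, the P<0.05 there concerns the later superiority test, and no interval is named for the 10-point margin. One-sided 0.05 is itself inferred, because it is what returns 53. The figures 63%, 67 and 79 are therefore conditional; the missing dropout allowance and the 74% do not depend on that interval.
- **Method.** The shortfall varies from about 3 to 9 points by method. This stands, so the result is best given as a range; every method tried falls below 80%.
- **Endpoint.** The calculation uses 9-month primary patency, while the primary outcome is 12-month TLR. The article gives no TLR rate, so 74% must not be read as the power of the primary comparison.
- **Lesions or patients.** The Abstract speaks of 106 patients, the sample size section of 106 lesions. With bilateral or multiple lesions, 106 patients could contribute more than 45 evaluable lesions per group, partly offset by correlation within patients. The 74% holds on the lesion reading.
- **Missing data.** Multiple imputation keeps dropouts in the analysis but does not restore the information lost with them.
- **Possible later adjustment.** Protocol amendments says the size may be adjusted on 12-month TLR. That makes 106 less final, but does not make the sentence correct.

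Two further inferences should be left out. Nothing in the document says that a failed noninferiority test would be read as evidence against CBE. The low power at equal true rates is a matter of the assumed 6.9-point advantage, separate from the dropout error.

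**Conclusion.** The statement is wrong as written. By the section's own inputs, 53 per group is the evaluable number at one-sided alpha 0.05, and no variant tried makes it the number after a 15% allowance. All inputs and the result are printed together, so this is not a detail left to a fuller document.

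The error is definite and moderate in size. The enrolment figure matching the claim is 62 to 63 per group instead of 53. With 53 enrolled and 45 evaluable, power is about 74% (roughly 71 to 77%), so the chance of missing noninferiority rises from 20% to about 26% when the planning assumptions are true. This rests on 106 lesions being enrolled, exactly 15% being lost, one-sided alpha 0.05, and true patency rates of 89.1% and 82.2%.

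**What to change.** In Sample size calculation:

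1. State that 53 lesions per group is the evaluable number for 80% power at one-sided alpha 0.05, and that with 15% dropout (45 evaluable per group) power is about 74%.
2. Label both as power for the assumed 9-month primary patency rates per lesion, and not for 12-month TLR.
3. State that alpha is one-sided.

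In Statistical analysis, name the interval that decides the 10-point margin. For one-sided 0.05 this is the two-sided 90% confidence interval for the risk difference. If a two-sided 95% interval is to be used instead, state about 63% power after dropout, and that 80% would need 67 evaluable per group (79 enrolled).

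The cost is a few sentences in two sections and a less favourable stated power. No extra enrolment is needed to correct the statement; enrolling more to recover 80% would be a separate decision.
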